##### Exclusion criteria

2.2.1.1

Only workers unwilling or unable to complete the assessments will be excluded.

Criteria of follow-up match the criteria for referral to a cardiovascular risk appointment by the Occupational Health physician. These criteria will be based on the Cardiovascular Prevention recommendations from 2021 of the European Society of Cardiology (ESC) and are as described in Table 1, regardless of whether there is a previous history of atherosclerotic disease. The combined use of the SCORE2 and SCORE algorithms reflects data availability in the OM setting: in the case of unavailability of HDL-cholesterol in the OM setting, the legacy SCORE algorithm is used as a pragmatic fallback, consistent with the flexibility allowed under the 2021 ESC guidelines (4, 11, 12).

**Table 1 T1:** Criteria for referral to a cardiovascular risk appointment by the occupational health physician, based on the cardiovascular prevention recommendations from 2021 of the European Society of Cardiology (ESC).

*Markedly elevated single risk factor*
• Total cholesterol >310 mg/dL or LDL cholesterol >190 mg/dL
• Blood pressure >180/110 mmHg
• Moderate or severe chronic kidney disease, defined as eGFR <60 mL/min/1.73 m^2^ (CKD-EPI 2021 creatinine equation)

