#### Data collection

2.2.4

Participants will be assessed in three time points:
at baseline, at their working company by Occupational Safety and Health Technician and by OM doctorat T0, at hospital centre by a medical doctor, for participants referred by the OM doctor based on their CV-risk levelat T12, at hospital centre by a medical doctor, 12 months after T0.Study variables to be used in this study, and related definitions, are described in the following subsections. Table 2 shows the set of data that will be collected and variable features. The main study variables concern demographics, habits, laboratory testing, comorbidities, medications and destination are listed below in more detail.

**Table 2 T2:** Data collection – variables and corresponding features.

Variable	Label	Evaluation period
Inclusion Criteria Check		
consentimento_informado	Signed informed consent	Baseline
avaliacao_possivel	Participant willing and able to complete the assessments	Baseline
Demographics and disease history		
ano_de_nascimento	Birth year	Baseline
sexo	Sex	Baseline
tabagismo_status	Smoking status	Baseline, T0, T12
dieta	Enter Diet Data?^a^	Baseline
sono	On average, how many hours of sleep do you get in a 24-hour period?^b^	Baseline
exercicio_fisico	How many minutes of moderate (or greater) intensity activity per week?^b^	Baseline
drc_moderada_grave	Presence of Moderate or Severe Chronic Kidney Disease	Baseline, T0, T12
dm	Presence of Diabetes Mellitus	Baseline, T0, T12
historia_evento_cv	History of Cardiovascular Event	Baseline, T0, T12
especificacao_eventos_cv	Specification of Cardiovascular Events	Baseline, T0, T12
outros_antecedentes	Other Pathological History	Baseline, T0, T12
Diet Questionnaire		
dieta_porcoes_vegetais_semana	How many servings of vegetables do you consume per week?	Baseline
dieta_porcoes_carne_vermelha_semana	Servings of Red Meat per Week	Baseline
dieta_porcoes_manteiga_creme_semana	How many servings of butter or cream do you consume per week?	Baseline
dieta_porcoes_graos_integrais_dia	How many servings of whole grains do you consume per day?	Baseline
dieta_consumo_fastfood_semana	Times Consuming Fast Food Meals per Week	Baseline
por_es_de_frutas_por_semana	How many servings of fruit do you consume per week?	Baseline
dieta_peixe_semana	How many servings of fish or shellfish/seafood do you consume per week?	Baseline
dieta_feijoes_semana	How many servings of beans do you consume per week?	Baseline

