dieta_doces_semana	How many servings of commercial sweets, candy bars, pastries, cookies, or cakes do you consume per week?	Baseline
dieta_bebidas_acucaradas_semana	How many servings of sugar-sweetened beverages do you drink per week?	Baseline
Usual Medication		
anti_dislipidemico	Anti-dyslipidemic	Baseline, T0, T12
anti_hta	Anti-hypertensive	Baseline, T0, T12
anti_agregantes	Anti-platelet	Baseline, T0, T12
farmaco_sem_medicacao	Without Usual Medication	T0, T12
farmaco_mh_dci	Drug (Previous Usual Medication) - International Nonproprietary Name (INN)	T0, T12
farmaco_mh_dose	Drug (Previous Usual Medication) - Dose	T0, T12
outro_farmaco	Insert another drug	T0, T12
Prescribed Medication		
intervencao	Was a new drug prescribed as a result of this assessment?	T0, T12
farmaco_intervencao_dci	Newly Prescribed Drug - International Nonproprietary Name (INN)	T0, T12
farmaco_intervencao_dose	Newly Prescribed Drug - Dose	T0, T12
outro_farmaco_intervencao	Insert another drug?	T0,T12
Clinical Evaluation		
ta_sist	Systolic Blood Pressure (mmHg)	Baseline, T0, T12
ta_diast	Diastolic Blood Pressure (mmHg)	Baseline, T0, T12
fc	Heart Rate (bpm)	Baseline, T0, T12
peso	Weight (kg)	Baseline, T0, T12
altura	Height (cm)	Baseline, T0, T12
Laboratory testing		
data_avaliacao_analitica	Date of Analytical Assessment	Baseline, T0, T12
colesterol_total	Total Cholesterol (mg/dL)	Baseline, T0, T12
ldl_c	LDL-C (mg/dL)	Baseline, T0, T12
hdl_c	HDL-C (mg/dL)	Baseline, T0, T12
triglicerideos	Triglycerides (mg/dL)	Baseline, T0, T12
hba1c	HbA1c (%)	Baseline, T0, T12
creatinina	Creatinine (mg/dL)	Baseline, T0, T12
egfr	Estimated Glomerular Filtration Rate (mL/min/1.73m^2^)	Baseline, T0, T12
ureia	Urea (mg/dL)	Baseline
lp_a	Lipoprotein (a)	T0
apo_a	Apolipoprotein A	T0, T12
apo_b	Apolipoprotein B	T0, T12
Destination		
destino_consulta_mo	Destination of the Participant	Baseline
destino_final_hospitalar	Destination After 12 Months of Hospital Follow-Up	T12
Medication adherence questionnaire		
qat_1_toma_hora	Do you always take your medication at the appropriate time?	T12
qat_2_sentir_mal	When you feel bad, have you ever discontinued taking your medication?	T12
qat_3_esquecer	Have you ever forgotten to take your medication?	T12
qat_4_esquecer_fds	Have you ever forgotten to take your medication during the weekend?	T12
qat_5_falha_semana	In the last week, how many times did you failed to take your prescribed dose?	T12

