6. Level of Adherence to Medication Prescribed in the Hospital CV Risk Consultation: Descriptive statistics will assess the adherence levels, measured by SMAQ among patients prescribed medications in the hospital CV risk consultations.
7. Proportion of Patients Who Attended Smoking Cessation Consultation: Descriptive statistics will determine the proportion of patients attending smoking cessation consultations over patients who were referred and participated in hospital CV risk consultation.
8. Change in distribution from Baseline in Various CV Risk Factors after 12 Months: Appropriate statistical methods will be used to calculate the distribution change from baseline (first hospital consultation) for the following CV risk factors after the use of this simplified referral process.
a. LDL-C
b. Blood pressure (SBP and DBP)
c. Moderate or severe chronic kidney disease
d. Smoking status
e. HbA1c
f. BMI
Statistical methods for this endpoint are specified in Section 2.3.1.
9. Distribution of Lipoprotein (a) at the first hospital consult: Descriptive statistics will assess the distribution of Lipoprotein (a) at the first hospital consult.
10. Prevalence of CV Risk Factors in the industrial/manufacturing in São João da Madeira: Appropriate statistical methods will be used to estimate the prevalence of CV risk factors within the industrial/manufacturing companies, including the levels of Lipoprotein (a) among very high CV risk individuals.
11. Proportion (%) of Identified Patients Referenced to GP Consultation: Descriptive statistics will be used to calculate the percentage of patients referred to GP consultations.

For the change in CV risk factors from baseline/T0 to T12, repeated continuous measures will be analyzed using linear mixed-effects models (or generalized estimating equations, as appropriate to the outcome distribution) with a random intercept per participant to account for within-subject correlation across the baseline, T0 and T12 assessments. Binary or categorical repeated measures will be analyzed using generalized estimating equations with a logit link. Models will be adjusted *a priori* for age, sex, baseline CV risk category, and baseline value of the outcome variable; additional covariates identified as clinically relevant confounders may be added in sensitivity analyses.

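### Endpoint 8c follows 12-month kidney change only as a yes/no CKD status, although eGFR is collected at every assessment; modelling continuous eGFR would keep far more information at no cost

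*Protocol article*

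**What the plan says.** All references are to the protocol article.

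- **Endpoint.** Table 3, endpoint 8, lists six risk factors for change over 12 months. LDL-C, blood pressure, HbA1c and BMI are measured quantities and smoking is naturally a category. The kidney item is "c. Moderate or severe chronic kidney disease". The starting point is the first hospital visit: the plan is to "calculate the distribution change from baseline (first hospital consultation").
- **Definition.** The only one is in the referral criteria (Table 1): "Moderate or severe chronic kidney disease, defined as eGFR <60 mL/min/1.73 m^2^ (CKD-EPI 2021 creatinine equation"). No repeat reading or persistence is required.
- **Data.** Table 2 has two separate fields, both at Baseline, T0 and T12. One is "Presence of Moderate or Severe Chronic Kidney Disease", under demographics and disease history. The other is "Estimated Glomerular Filtration Rate (mL/min/1.73m^2", under laboratory testing. Section 2.2.6 has the hospital doctor record disease history at T0 and T12.
- **Model.** Section 2.3.1 states: "Binary or categorical repeated measures will be analyzed using generalized estimating equations with a logit link". For the others, "repeated continuous measures will be analyzed using linear mixed-effects models", or GEE where the distribution calls for it. All models adjust for age, sex, risk category at baseline and the outcome's own baseline value.
- **Standing.** Section 2.2.2 calls the 12-month risk-factor analyses exploratory and unpowered. They are meant to help design and size a later study.

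**The concern.** The kidney item is the only one in endpoint 8 for which a collected continuous measurement is set aside in favour of a class. A fall in eGFR from 85 to 70, or a rise from 40 to 55, leaves the status unchanged. Only movement across 60 counts, and most attendees may be far from 60. Two things are at stake. First, the study would have little ability to describe a real change in kidney function from data it already holds. Second, the adjusted logit GEE may rest on few people with CKD. The stated purpose of these analyses also suffers: planning a later study needs a mean change and its SD, which a status with few transitions cannot supply.

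**Working it through.** **The plan's own figure.** The only sample-size figure is the margin of error for a prevalence of 15% with 1000 people: 1.96 × √(0.15 × 0.85 / 1000) = 0.0221, which reproduces the stated 2.2%. The expected hospital cohort is 0.15 × 1000 = 150, as stated. No figure is given for endpoint 8c.

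**Inputs.** From the protocol: n = 150, the cut-off of 60, and one eGFR field per assessment. Assumed, because the documents do not give them: true eGFR among attendees with mean/SD 90/15, 80/18 or 75/20; within-person CV of one reading of 5%, 8% or 10%; a true rise of 3 mL/min/1.73 m² in everyone; all 150 seen at T12; status derived from that visit's reading.

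**Method.** Simulate 1,000,000 people per scenario, each with one reading at T0 and one at T12. For each analysis take the mean within-person change divided by its SD, δ. Power at two-sided 5% is Φ(δ√150 − 1.96). Relative efficiency of status against continuous eGFR is (δ_status / δ_eGFR)². These are unadjusted paired comparisons.

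| Mean/SD | CV | CKD at T0, of 150 | Power, status | Power, eGFR | Relative efficiency |
|---|---|---|---|---|---|
| 90/15 | 5% | 3.8 | 17% | >99% | 0.03 |
| 90/15 | 8% | 4.6 | 14% | 94% | 0.06 |
| 90/15 | 10% | 5.4 | 13% | 79% | 0.09 |
| 80/18 | 5% | 20.8 | 48% | >99% | 0.09 |
| 80/18 | 8% | 22.0 | 34% | 97% | 0.16 |
| 80/18 | 10% | 23.2 | 29% | 88% | 0.21 |
| 75/20 | 5% | 34.8 | 58% | >99% | 0.11 |
| 75/20 | 8% | 35.8 | 44% | 98% | 0.19 |
| 75/20 | 10% | 36.9 | 36% | 91% | 0.24 |

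**Hand check of one cell (90/15, CV 10%, eGFR).** The variance of the difference is 0.10² × [(90² + 15²) + (93² + 15²)] = 0.01 × 17,199 = 172, so the SD is 13.1. Then δ = 3 / 13.1 = 0.229 and power = Φ(0.229 × 12.25 − 1.96) = Φ(0.84) = 80%, against 79% simulated.

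**A fall instead of a rise.** A separate simulation used 100 people, mean 82, SD 18, within-person SD 3 to 7 and a 3-unit fall (also assumed). It gave 86 to 100% with eGFR and 20 to 35% with the status.

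**No true change.** In the nine scenarios, 11 to 50% of those below 60 at T0 read 60 or more at T12. That is about 1 to 8 people per 150. In each scenario the same number, 1 to 8, cross the other way, so the expected net change in the proportion is zero.

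**The case against.** A reader might infer that the plan would report recovery from a chronic condition when there is only measurement noise. The documents do not support that, for two reasons.

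- Nothing says the T0 or T12 status is computed from that visit's eGFR. The definition sits in the referral table; the status is a disease-history item that a doctor records. If it is an established diagnosis, it will not flip with each result.
- Even if it is derived from single readings, endpoint 8 concerns change in distribution and the GEE estimates a population-average change. With no true change, false recoveries and false new cases cancel. Only individual transitions would mislead.

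Both points stand. They do not rescue the status as an outcome: an established diagnosis will scarcely change in 12 months, so 8c would then measure almost nothing.

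Regression to the mean is a possible further argument, since an eGFR below 60 at the OM visit is itself a ground for referral and the model includes that visit. But it would affect continuous eGFR too, so it is no argument for one scale over the other.

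The endpoint is also declared exploratory, no 3-unit change is hypothesised, and eGFR would presumably be covered by the general descriptive summaries of continuous variables. This limits the weight of the point. It does not supply a modelled eGFR change, and low power from a small sample is a different matter from setting aside data already collected.

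**Conclusion.** The point holds as one of efficiency, and it is minor. Analysing 8c only as a status retains about 3 to 24% of the information in continuous eGFR, a loss of 76 to 97%. For a true 3-unit shift in 150 attendees, power is about 13 to 58% against 79% to over 99%. With about 4 to 37 CKD cases at T0, the adjusted logit GEE may have few events; at the lower end clearly so, at the upper end less so. The sizes rest on assumed eGFR distributions, CVs, shift and complete follow-up, and on a status derived from single readings. The direction is the same in every scenario tried. A claim that the plan would produce false remission in its planned summary is not supported.

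**What to change.** - In Table 3, make T0-to-T12 change in continuous eGFR the main analysis of 8c, in the linear mixed model already planned for LDL-C and blood pressure.
- Keep CKD status as a descriptive T0 and T12 summary. State whether it is derived from eGFR or recorded by the physician.
- State that the contrast of interest is T0 to T12. Continuous eGFR does not remove regression to the mean from the OM visit.

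The cost is wording only. eGFR is already in Table 2 at all three assessments, no visit or test is added, and the referral criterion is unchanged.

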**Figure 1 F1:**
[figure not shown]
Overview of patient participation and data collection. OM: Occupational Medicine; CV: cardiovascular; T0: first hospital consultation; T12: 12-month hospital consultation; a) CV risk consultation and/or Smoking cessation consultation, when applicable; b) Risk prediction algorithms: SCORE2 for patients aged 40 years or more with HDL available; SCORE for patients aged 40 years or more without HDL available; c) Risk prediction algorithms: SCORE2 for patients aged 40 years or more. The enrollment phase includes the OM consultations occurring in the identified companies. The follow-up phase includes the hospital appointments occurring in ULSEDV.

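### Endpoint 8 has two inconsistent reference visits, and if the selecting OM value served as reference, regression to the mean could be reported as 12-month change

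*Protocol article*

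**What the plan says.** Table 3, endpoint 8, will "calculate the distribution change from baseline (first hospital consultation) for the following CV risk factors", listing LDL-C, blood pressure, chronic kidney disease, smoking status, HbA1c and BMI. The legend of Figure 1 gives "T0: first hospital consultation", so on this definition the reference is T0. Table 3 refers the reader to Section 2.3.1 for the methods.

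The model paragraph there states "For the change in CV risk factors from baseline/T0 to T12, repeated continuous measures will be analyzed using linear mixed-effects models", "with a random intercept per participant to account for within-subject correlation across the baseline, T0 and T12 assessments". The models are adjusted for age, sex, "baseline CV risk category, and baseline value of the outcome variable". The visit that supplies this covariate is not named.

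Section 2.2.4 uses the same word for a different visit: participants are assessed "at baseline, at their working company by Occupational Safety and Health Technician" and by the OM doctor, with T0 and T12 at the hospital as separate later time points. Table 2 follows that usage.

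Only workers referred from OM go on to T0. Table 1 gives the criteria: "Total cholesterol >310 mg/dL or LDL cholesterol >190 mg/dL", blood pressure above 180/110 mmHg, eGFR below 60, or a SCORE2 or SCORE threshold. No control group is described. Section 2.2.2 declares the risk-factor analyses exploratory and intended to inform the design and sample size of a later powered evaluation.

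**The concern.** Within one section *baseline* has two meanings for the same endpoint. In Table 3 it is T0. In the model paragraph it must be the OM visit, because T0 is listed beside it. An analyst could estimate T12 minus T0, T12 minus OM, or a change from both earlier visits pooled, and cite the protocol for each.

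The choice matters because the OM value selects the patient. Three of the selecting variables are endpoint 8 outcomes: LDL-C (8a), blood pressure (8b) and kidney disease (8c). A group chosen for extreme readings is expected to read closer to its own mean at the next measurement, with no intervention. Setting and assessor also change between OM (workplace, recorded by the technician) and T0 (hospital doctor), whereas T0 and T12 share both.

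Section 2.1.3 makes this 12-month change the Effectiveness dimension of RE-AIM. An inflated change carried into the planning of the next study would make that study too small. Section 2.4 does not list regression to the mean among its three main limitations.

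**Working it through.** **The plan's own figure.** The only computed figure is the margin of error in Section 2.2.2: 1.96 × √(0.15 × 0.85 / 1000) = 0.0221, which reproduces the stated 2.2%. Also 0.15 × 1000 = 150 expected appointments, as stated. The point does not depend on the margin, but the 1000 and the 150 are used below.

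**Assumed inputs.** The protocol gives no mean, SD or visit-to-visit correlation (ρ). Assumed: LDL-C mean 130, SD 35 mg/dL; SBP mean 130, SD 17 mmHg; normal distributions; ρ from 0.6 to 0.9. The cut-offs 190 and 180 are from Table 1.

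**Formulas.** With z = (cut-off − mean)/SD, the share selected is 1 − Φ(z) and the mean of those selected is mean + SD × φ(z)/(1 − Φ(z)). The expected fall at the next measurement with no effect is (1 − ρ) × (selected mean − mean).

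**LDL-C above 190.** z = 60/35 = 1.71. Share selected 0.043, about 43 of 1000. Selected mean 204.3, which is 74.3 above the assumed mean.

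| ρ | Fall with no effect (mg/dL) |
|---|---|
| 0.6 | 29.7 |
| 0.7 | 22.3 |
| 0.8 | 14.9 |
| 0.9 | 7.4 |

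Averaged over 150 referred patients, this route alone gives 14.9 × 43/150 = 4.3 (ρ = 0.8) to 22.3 × 43/150 = 6.4 mg/dL (ρ = 0.7).

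**SBP above 180.** z = 50/17 = 2.94. Share selected 0.0016, about 1.6 of 1000. Selected mean 184.9. The fall is 11.0 mmHg at ρ = 0.8 and 22.0 at ρ = 0.6, but over 150 patients it is 11.0 × 1.6/150 = 0.1 to 22.0 × 1.6/150 = 0.2 mmHg.

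**Score entrants.** For the top 15% on a score correlated r with a given factor, the fall is (1 − ρ) × r × φ(z)/0.15 in SD units, where φ(z)/0.15 = 1.55. With r = 0.3 and ρ = 0.9 it is 0.05 SD; with r = 0.5 and ρ = 0.6 it is 0.31 SD.

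**Does the stated model remove it?** In a simulation with no treatment effect (LDL-C, ρ = 0.8, selected at OM above 190), visit means were about 204 (OM), 189 (T0) and 190 (T12).

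| Contrast | Change (mg/dL) |
|---|---|
| T12 − OM | −14.6 |
| T12 − mean of OM and T0 | −7.1 |
| T12 − T0 | +0.4 (simulation noise) |

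A random-intercept model with the OM value as covariate and all three visits as outcomes still gave about −14 for T12 against OM. The covariate does not remove the artefact.

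**Scale.** At ρ = 0.8 the standard error of a paired LDL-C change in 150 patients is 35 × √(2 × 0.2)/√150 = 1.8 mg/dL. Even the diluted 4.3 mg/dL is 4.3/1.8 = 2.4 standard errors.

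**The case against.** The strongest reply is that Table 3, which defines the endpoint, already names T0, and that *baseline/T0* can be read as repeating that equation. Entering the OM value as a repeated measure does not make T12 minus OM the reported contrast, and the exact contrast could sit in an analysis plan that is not shown. This stands in large part. A reader might infer that the plan will count regression to the mean as effect; the documents do not support that. They support only that the wording permits it. The contradictory wording is a finding, because the article states the reference twice and differently.

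Second, the large falls belong to single-threshold entrants and not to endpoint 8 as a whole. This stands: on these assumptions the SBP figure describes one or two workers, and the LDL-C figure shrinks to about 4 to 6 mg/dL over all referred patients before any contribution from score entrants. HbA1c and BMI are not Table 1 criteria, so little is expected there.

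Third, T0 minus OM should not be written off as pure artefact. Under Section 2.2.12 the OM doctor may give advice or refer to Family Medicine, so real change can occur before T0. This also stands.

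Fourth, the endpoint is declared exploratory and unpowered. That lowers the stakes, but the stated use in planning a later study keeps some.

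**Conclusion.** The inconsistency is real and in the current text. Its consequence is conditional: bias arises only if the OM value is used as, or pooled into, the reference. It would then be direct for LDL-C, blood pressure and kidney disease, weaker for patients entering through SCORE or SCORE2, and small for HbA1c and BMI. For LDL-C the size is about 15 to 22 mg/dL in those selected on that threshold, or 4 to 6 mg/dL over 150 referred patients from that route; for SBP it is negligible overall. All of this rests on assumed means, SDs and correlations, and on 150 of 1000 workers being referred and measured.

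The baseline-value covariate is a second fault in the same paragraph. Whether it comes from OM or T0, that measurement is also one of the repeated outcomes.

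T12 minus T0 is free of the selection artefact only if visit errors are independent, and without a control group it remains a before-after change. This is a cheap correction to an exploratory analysis; the primary objective is not touched.

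**What to change.** - Align the model paragraph with Table 3: T12 minus T0 is the only reported 12-month change for endpoint 8, described as an uncontrolled before-after change.
- Resolve the covariate in one of two ways. Either state that it is the OM value and take OM out of the outcome vector, or keep OM as an outcome and drop the baseline-value covariate. No measurement should be both.
- Report T0 minus OM separately and descriptively, noting that it mixes regression to the mean, change of setting and any real change after the OM visit.
- Give the OM visit its own name throughout, so that *baseline* has one meaning.
- Add regression to the mean to the limitations in Section 2.4.

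The cost is wording and the choice of contrast. No new data or visits are needed. If the OM visit would otherwise have been the reference, the reported changes are likely to look less favourable. The change should be made before the data are analysed, since a later choice of reference would look data-driven.

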### Study design and setting

2.2

Prospective pilot project for the integration of services, with a pragmatic design. Data collection lasts for 18 months in two distinct phases (Figure 1):
A cross-sectional 6-month intervention phase to enroll patients and operationalize the primary objective and secondary objectives 1, 2 and 5. This is to implement a process to promote the access to cardiovascular risk hospital appointments, through the systematic identification of very high CV risk patients in appointments from Occupational Health carried out on workers from the industrial/manufacturing companies of the municipality of São João da Madeira.A longitudinal, clinical follow-up phase, lasting 12 months, to assess secondary objectives 3 through 6. This is to estimate pharmacological therapy adherence and the impact on cardiovascular risk profile after the intervention above mentioned.

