#### Sample size

2.2.2

Based on prior publications (7, 12, 13), it was estimated that up to 15% of the studied population has at least 1 of the inclusion criteria for referral (very high cardiovascular risk), so there is the expectation to perform 150 cardiovascular risk appointments in the first 6 months of the project (6–7 appointments/week, divided into two weekly periods of 4 h).

In this sense, instead of a sample size calculation, a precision estimation was calculated: for a confidence interval of 95%, a prevalence of 15% and 1000 persons included, a margin of error of 2.2% is estimated. This precision-based estimate addresses the primary objective and the descriptive prevalence outcomes (secondary objectives 1, 2 and 5), for which the expected sample provides adequate precision. As a pilot implementation study, CARDIOGAP + is not powered to test a pre-specified hypothesis regarding the magnitude of risk-factor change; these analyses are exploratory and hypothesis-generating, intended to inform the design and sample size of a future, adequately powered evaluation.

The sample size may be adjusted to the participation of physicians from Occupational Health and participating companies, with ULSEDV having the capacity to accommodate more referrals.

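### With a random intercept as the only stated dependence across three visits, the 95% interval for the T0-to-T12 change can be too narrow for slowly varying continuous outcomes

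*Protocol article*

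**What the plan says.** Table 3, endpoint 8, sets out to "calculate the distribution change from baseline (first hospital consultation) for the following CV risk factors" after 12 months. The contrast is therefore T0 to T12. The continuous outcomes are LDL-C, systolic and diastolic blood pressure, HbA1c and BMI.

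The text after Table 3 (section 2.3.1) specifies the dependence between visits: the model is to be fitted "with a random intercept per participant to account for within-subject correlation across the baseline, T0 and T12 assessments". Three assessments are thus modelled for a two-visit endpoint. The same sentence leaves some choice of model class for these outcomes, namely "linear mixed-effects models (or generalized estimating equations, as appropriate to the outcome distribution"). The covariates are age, sex, "baseline CV risk category, and baseline value of the outcome variable". No residual covariance, random slope or type of standard error is given.

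For the remaining endpoint 8 outcomes, "Binary or categorical repeated measures will be analyzed using generalized estimating equations with a logit link".

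On timing, section 2.2.4 puts T12 twelve months after T0. The OM-to-T0 interval is not given. Section 2.2 describes "A cross-sectional 6-month intervention phase to enroll patients", and section 2.2.2 says "there is the expectation to perform 150 cardiovascular risk appointments in the first 6 months of the project". Section 2.2.2 also declares the risk-factor changes exploratory and unpowered, and says they should inform the design and size of a later study.

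**The concern.** A random intercept with independent residuals implies compound symmetry: equal variance at each visit and equal variance of every pairwise difference. The design gives reason to doubt this. One interval is the wait for a hospital appointment. The other lasts 12 months and begins where the hospital doctor may prescribe new drugs to some patients and not others. Patients' 12-month changes may well differ from one another more than their OM-to-T0 changes do.

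If so, the model averages a small variance into the error of the contrast that matters. With complete data the estimated mean change is unaffected, because it is still the difference between the T12 and T0 means. Only its standard error and interval are wrong. For a pilot, an estimate with an honest interval is the main product of endpoint 8, so this matters even without a formal test.

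**Working it through.** **The plan's own figure.** The only precision figure stated is a 2.2% margin for a 15% prevalence in 1000 persons: 1.96 × √(0.15 × 0.85 / 1000) = 0.0221. It reproduces, and 15% × 1000 = 150 gives the expected appointments. It concerns prevalence; no precision is stated for the 12-month change.

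**Formula.** Let v1, v2 and v3 be the between-patient variances of the changes OM–T0, T0–T12 and OM–T12. With three complete visits and visit as a factor, the squared deviations from a participant's own mean sum to one third of the three squared pairwise differences. On 2 degrees of freedom per participant the residual variance is (v1 + v2 + v3)/6. The model gives every change twice that, (v1 + v2 + v3)/3, where the correct value for T0–T12 is v2. Define

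R = (v1 + v2 + v3) / (3 v2).

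The model's standard error is √R times the correct one, and the true two-sided error at nominal 5% is 2[1 − Φ(1.96 √R)]. The interval is too narrow when the mean of v1 and v3 is below v2, and too wide when it is above.

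**Limit.** With v1 = 0 and v3 = v2, R = 2/3 and √R = 0.816. The standard error is 18% too small, the error 10.95% and coverage about 89%.

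**Scenarios.** The documents give no variances, so all of these are assumptions. Let r = gap/12, with the OM-to-T0 gap in months.

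| Assumed pattern | R | 1 month | 3 months | 6 months |
|---|---|---|---|---|
| Slow drift (random walk), no visit noise | 2(1 + r)/3 | 9.6% | 7.4% | 5.0% |
| Same drift, half of v2 is visit noise | (2.5 + r)/3 | 6.9% | 6.1% | 5.0% |
| Person-specific linear trends | 2(1 + r + r²)/3 | 9.5% | 6.7% | 3.4% |

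For example, slow drift at 3 months has r = 0.25, R = 0.833 and 1.96 × 0.913 = 1.789, hence 7.4%.

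If instead patients are stable up to T0 and their responses then spread out, with visit noise SD s and response SD h, then v1 = 2s² and v2 = v3 = 2s² + h²:

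| Assumed outcome | s | h | R | Error |
|---|---|---|---|---|
| BMI-like | 0.3 | 1.2 | 0.704 | 10.0% |
| HbA1c-like | 0.15 | 0.4 | 0.740 | 9.2% |
| LDL-C-like (mg/dL) | 12 | 25 | 0.772 | 8.5% |
| Systolic pressure-like (mmHg) | 9 | 8 | 0.906 | 6.2% |

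**Simulation (n = 150, true T0–T12 change zero).** A fitted random-intercept model with a 1-month gap and 5% visit noise rejected in 10.3% of 400 data sets; GEE with robust standard errors rejected in 5.8%. In closed-form runs of 4,000 per setting, adding the OM value as covariate while keeping the OM row as a response did not remove the excess (10.2% at 0.5 month, 9.1% at 1 month, no visit noise). A paired T0/T12 analysis gave 4.3–5.7%, and a random-intercept model with only the T0 and T12 rows 4.4–5.9%.

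**The case against.** **The size is unknown.** The protocol states no OM-to-T0 interval and no SD. Doubling an assumed OM–T0 SD shows the sensitivity. With independent changes, R = 2(1 + r)/3 with r = v1/v2. LDL-C change SDs of 14 and 45 mg/dL give 9.4%; 28 and 45 give 5.9%. This stands. The enrolment schedule offers only a loose bound: if T0 visits are spread evenly over the 6 months and OM visits fall in the same phase, the mean gap is at most about 3 months. Baseline laboratory results carry their own date and are recorded before the OM appointment, so the laboratory gap may be longer.

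**The OM-to-T0 period need not be quiet.** Section 2.2.12 allows advice or referral to Family Medicine at the OM visit, usual medication is already recorded there, and setting and assessor change between the two visits. A reader might infer a short, untreated and nearly noise-free interval. The documents state none of these.

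**No test is planned.** Endpoint 8 has no hypothesis or significance level, so a false-positive rate matches no planned decision. This stands too; interval coverage is the relevant measure.

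**The wording leaves room.** An article may leave residual covariance and standard errors to a fuller plan, and GEE is allowed. But the dependence structure is named, not omitted, and GEE is invoked by outcome distribution, so roughly normal outcomes stay with the random intercept. If the baseline value were only a covariate and T0 and T12 the only responses, the problem would vanish. The text, however, places the random intercept across all three assessments.

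**Carry-over to a later study is uncertain.** Descriptive SDs will also be reported, and nothing says the model's variance would be used for planning.

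**Conclusion.** The point holds as a conditional one. The stated model ties the error of the T0-to-T12 change to a visit outside that contrast. Where OM-to-T0 changes are clearly less variable, coverage of the 95% interval can fall to about 89–93%. This is most plausible for BMI, HbA1c and LDL-C with a gap of up to roughly 3 months and little visit noise. Blood pressure is likely to be affected less, with an error of about 6–7%.

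A reader might infer that the plan doubles the error rate for slowly varying outcomes. The documents do not support that: 11% is the limit as v1 approaches zero, the excess disappears under slow drift at a 6-month gap, and with person-specific trends at that gap the interval is too wide (error 3.4%). Chronic kidney disease and smoking status are analysed by GEE and are not affected. The calculations assume complete data. Because the analyses are exploratory, this is an inexpensive improvement to the analysis, not a threat to the study's main purpose.

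**What to change.** In section 2.3.1, treat visit as a categorical factor with an unstructured 3 × 3 within-participant covariance (REML, Kenward-Roger degrees of freedom), and report the T12–T0 contrast from that model. Either of two alternatives would also do: keep the random intercept but use robust (sandwich) standard errors, or use only T0 and T12 as response rows.

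The cost is one sentence and no new data. The unstructured matrix has 6 parameters against 2 for compound symmetry, so 4 more, which is minor with about 150 participants expected at T0. Intervals for some outcomes will become somewhat wider.
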